#### Sample size consideration

A sample size of 382 patients was estimated in order to have 90% power to detect a difference in SBP of 5 mmHg (SD 15 mmHg) between the intervention and the control group with a contrast of two-tailed hypotheses and an alpha error of 0.05. This figure represents a clinically relevant difference (which should represent a reduction of approximately 19% in strokes) and is in line with the results observed in previous trials in this field (TASMINH2 and TASMINH-SR) [15, 16]. These figures will be increased by 20% to compensate for possible drop-outs and follow-up loss, resulting in a total sample size of 458 participants.

### Intervention

#### Intervention group

##### Blood pressure self-monitoring

Patients will be trained to perform SMBP by the research team through a validated home blood pressure monitor (Omron model M3 HEM-7131-E). Patients will take their BP in the morning and in the afternoon, every day of the first week of each month. This will be done in the morning, before breakfast and before taking their medication (between 6 am. and 9 am.) and in the evening before dinner and before taking their medication (between 6 pm. and 9 pm.). These measurements will be recorded by the patients for the first seven days of each month on the “monthly registration sheets” located in the “*Intervention group booklet*”. If patients want to monitor their BP during the remaining weeks of the month, it is recommended that they just do so one day a week. Patients are instructed to act according to a table that contains easy-to-follow colour coded action steps. This guideline prompts the patient to contact the GP or visit the health center when BP values are very high or very low. Four or more above target readings in a month will require a change in medication (See Fig. 2).

##### Target blood pressure

Patients will be informed of their target BP, which will be established by their own GP and individualized for each patient based on the *Guidelines for the management of arterial hypertension of the European Society of Hypertension (ESH) and European Society of Cardiology (ESC)* [19]*.* Recommendations on target BP, according to cardiovascular risk and reflecting home as compared to office readings are shown in Table 1.

**Table 1 Tab1:** Target blood pressure, according to cardiovascular risk conditions

Age	Clinical situation	TARGET BLOOD PRESSURE			
		SBP		DBP	
		SMBP	Office readings	SMBP	Office readings
< 80 years old	Without increased cardiovascular risk	≤135	≤140	< 85	< 90
	Diabetes	< 135	< 140	< 80	< 85
	Cerebrovascular disease (previous stroke or TIA)			< 85	< 90
	Coronary Heart Disease				
	Peripheral artery disease				
	Chronic kidney disease				
≥ 80 years old		< 145	< 150	< 85	< 90

*SBP* Systolic blood pressure, *DBP* Diastolic blood pressure, *SMBP* Self measured blood pressure

Modified from the *2013 ESH/ESC Guidelines for the management of arterial hypertension*. The European Society of Hypertension (ESH) and European Society of Cardiology (ESC)

##### Self-titration

In order to reach their target BP, each patient will be given a self-management plan to adjust medication if necessary depending on blood pressure measurements (See Fig. 2). The self-adjustment plan will consist of either an increase in the dose or additional medication. Therapeutic plan choice will be at the discretion of the GP, who will receive a copy of the Clinical Practice Guidelines of the European Society of Cardiology [19] to aid decision-making. If self-adjustment takes place, the participant will have an appointment with his/her GP within 3 weeks following self-adjustment, and a new tailored self-management plan will be provided.

#### Control group

Patients allocated to the control group will receive routine hypertension care with appointments and medication changes following the GP’s criteria in the context of routine clinical practice.

In both, the intervention and control group, all relevant concomitant care within usual clinical practice will be at the discretion of the GP.

### Outcomes

The primary outcome will be the change in mean SBP -mmHg- between baseline and 12 months.

Secondary outcomes will include:Change in mean SBP at 6 and 24 months of follow-up.Change in mean DBP at 6, 12, and 24 months of follow-up.Percentage of patients with SBP < 140 mmHg and DBP < 90 mmHg at 6, 12 and 24 months of follow-up.Quality of life (as measured by EuroQoL-5D) at 6, 12 and 24 months of follow-up.Adherence measured by proportion of days covered (PDC) at 6 and 12 months of follow-up.Persistence, defined as period of continuous use of the corresponding drug from the beginning of the follow-up until its discontinuation at 6 and 12 months of follow-up.Therapeutic inertia (TI), defined as the number of patients whose pharmacological treatment had not been modified, divided by the number of patients not reaching the target values (SBP and/or DBP measurements taken at 6 and 12 months of follow-up), ​​according to the recommendations of the European Society of Hypertension and European Society of Cardiology [19].

Other outcome measures:Changes in lifestyle (smoking, exercise, body weight) at 6, 12, and 24 months compared to these characteristics at baseline.Clinical events: We will assess if any of the following adverse events are present during the follow-up: angina, myocardial infarction, stroke, hypotensive crisis and death.Use of health services for hypertension at 6, 12 and 24 months.Incremental cost per quality-adjusted life year gained in the intervention group compared to the control group.Views and experiences of patients and health professionals on the self-management (SMBP plus self-titration) of hypertension.

### Data collection

Data will be collected at the different participant study sites. Details on type of data and timing of collection are shown in Fig. 1.   

Data entry, coding, security, and storage, including any related processes to promote data quality (eg, double data entry, etc) and other aspects related to data management such as data monitoring of the ADAMPA study, will be performed by the SCReN platform (for more information on the Screen platform and its role regarding the ADAMPA study, see: https://www.scren.es/, and https://www.scren.es/proyectos.php).

### Statistical analysis

Analysis will be on an intention-to-treat basis for complete cases. We will use mixed models (general linear modeling –GLM) to compare SBP at 12 months between the intervention and control groups. This analysis will be presented in both crude and adjusted forms for the different covariates of interest (baseline BP, gender, GP/PCC-random effect, diabetes, etc.). A sensitivity analysis will be performed to examine the potential effect of missing data, which will include substitution by multiple imputation, replacement of data lost by the most recent data or by the mean of the series. Additionally, analyses of the main outcome measure by subgroups of age, gender, comorbidity, level of chronicity, better control at baseline, etc. will be performed.

Differences in secondary outcome measures (DBP, percentage of patients controlled, PDC, persistence and TI) will be analyzed using methods similar to those used for analysis of the main outcome measure.

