## Methods

### Study design and setting

The ADAMPA study is a pragmatic, controlled, randomized, unblinded clinical trial with two parallel groups assigned in a ratio of 1:1 to self-management (which includes educational components, SBMP and self-titration of antihypertensive medication based on a patient’s GP’s pre-established adjustment plan) or to usual care (with educational components too).

All participants belong to a Health Area in the Valencia Region (Spain), with a population coverage of 345,500 inhabitants and a geographical area covering the north-east of the city of Valencia and some surrounding towns that are served by sixteen Primary Care Centers (PCC), two Hospitals and a Medical Specialty Centre.

This trial has been registered in the https://eudract.ema.europa.eu/ database with reference number EudraCT: 2016–003986-25.

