**Fig. 3 Fig3:**
[figure not shown]
Participants’ flow through the study. *GP* General Practitioner, *SBP* Systolic Blood Pressure, *DBP* Diastolic Blood Pressure, *BP* Blood Pressure, *SMBP* Self-Management of Blood Pressure

Patients have the right to leave the study at any time. In addition, the researcher may discontinue a patient from the study if deemed necessary for any reason including: non-eligibility (retrospective if not detected at the time of inclusion, or prospective e.g. pregnancy during the follow up), an adverse event or disease progression involving incapacity to comply with trial procedures.

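### The primary analysis is called intention-to-treat but keeps only patients with a 12-month SBP and leaves the 6-month SBP unused, so the effect estimate is open to bias from unequal loss

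*Protocol article*

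**What the plan says.** The Statistical analysis section sets the analysis set in one sentence: "Analysis will be on an intention-to-treat basis for complete cases". The main comparison is of SBP at 12 months, by mixed models, in crude and adjusted forms. The named covariates are baseline BP, gender and diabetes, with GP or primary care centre as a random effect; the list ends open. Neither a repeated-measures structure nor 6-month SBP is named.

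Missing data are handled in a sensitivity analysis: multiple imputation, and "replacement of data lost by the most recent data or by the mean of the series".

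Four other places bear on the point:
- Study design and setting: the trial is a "pragmatic, controlled, randomized, unblinded clinical trial with two parallel groups".
- Participant flow (control group text) and Outcomes: both arms attend a 6-month visit, and SBP change at 6 months is a secondary outcome.
- Sample size consideration: numbers are raised by 20% for drop-out and loss.
- Text below Fig. 3: "Patients have the right to leave the study at any time", and "the researcher may discontinue a patient from the study if deemed necessary for any reason". The listed reasons are non-eligibility ("retrospective if not detected at the time of inclusion, or prospective e.g. pregnancy during the follow up") and "an adverse event or disease progression involving incapacity to comply with trial procedures".

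**The concern.** Intention-to-treat means that all randomised patients are analysed as allocated. Restricting to complete cases keeps the allocation but not all the patients, so the label and the analysis set do not agree.

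The restriction is harmless only under a condition. The crude comparison is unbiased if missingness depends on arm alone. The adjusted one is unbiased if missingness depends only on arm and the covariates in the model. Neither allows for missingness that depends on how blood pressure developed after randomisation. The 6-month SBP is the measured variable most likely to carry that information. Adding it as a covariate to the 12-month model would not be a cure, because it is itself affected by treatment. It has to enter as an outcome or in an imputation model.

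In an unblinded trial whose arms ask different things of patients, loss related to both arm and blood pressure is a realistic possibility. If intervention patients with high SBP are the ones lost, the intervention looks better than it is.

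**Working it through.** **1. The plan's own figures.** Inputs from Sample size consideration: difference 5 mmHg, SD 15, two-sided alpha 0.05, power 90%.
- Normal approximation: n per arm = 2 × (1.960 + 1.282)² × 15² / 5² = 189.1, so 190 per arm and 380 in total.
- Two-sample t version: 190.1, so 191 per arm and 382 in total, as stated.
- Inflation: 382 × 1.2 = 458.4, stated as 458, or 229 per arm.
- At 20% loss: 458 × 0.8 = 366 complete cases, with power about 89%.

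Power is barely affected. The issue is bias.

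**2. Bias of completers by direct arithmetic.** Let d be the proportion missing in an arm, and g the mean 12-month SBP of its missing patients minus that of its completers. The full arm mean equals the completers' mean plus d × g, so for intervention minus control

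bias = -(d_I × g_I - d_C × g_C).

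The SE is 15 × √(1/n_I + 1/n_C), with n_I and n_C the completers out of 229 per arm. At 20% loss in each arm this is 15 × √(2/183.2) = 1.57. Two-sided type I error is Φ(-1.96 - bias/SE) + Φ(-1.96 + bias/SE). The document gives neither d by arm nor g, so the values below are assumptions.

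| Missing I / C | Gap I / C (mmHg) | Bias (mmHg) | Type I error |
|---|---|---|---|
| 20% / 20% | 5 / 5 or 10 / 10 | 0 | 0.05 |
| 20% / 20% | 5 / 0 | -1.0 | 0.10 |
| 20% / 20% | 10 / 0 | -2.0 | 0.25 |
| 20% / 20% | 15 / 0 | -3.0 | 0.48 |
| 25% / 15% | 5 / 5 | -0.5 | 0.06 |
| 25% / 15% | 10 / 10 | -1.0 | 0.10 |

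A 15 mmHg gap is a full SD and is an extreme case.

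**3. Simulation with baseline adjustment.** Assumptions: 229 per arm, SD 15, correlation 0.6 between 6- and 12-month SBP, true effect 0, ANCOVA on complete cases. Loss is about 22% to 23% in the intervention arm and 17% in control. In the arms named below, the odds of loss depend on 6-month SBP; otherwise loss is at random.
- Intervention arm only, odds ratio 1.8 per 10 mmHg: bias -0.9 to -1.6 mmHg and type I error about 9% to 18%, as the assumed correlation with baseline falls from 0.5 to 0.
- Intervention arm only, odds ratio 1.3, baseline correlation 0.5: bias about -0.4 mmHg, type I error little above nominal.
- The 1.8 dependence in both arms, baseline correlation 0.5: bias about -0.2 mmHg; with 20% loss in each arm, 0.
- Dependence reversed, with low-SBP intervention patients leaving, baseline correlation 0.5: bias about +0.9 mmHg, against the intervention.

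Under the 1.8 scenario, imputing by arm from baseline and 6-month SBP brought the estimate to within about 0.1 mmHg of the truth. That is expected, because missingness was made to depend on a variable in the imputation model. It shows what the 6-month data can repair, not that all loss is of this kind.

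**The case against.** Four counter-arguments carry weight.

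*Multiple imputation is already planned.* This is true, and if it includes 6-month SBP it would expose bias of the kind simulated. What remains is which result is the headline: the plan gives that place to the analysis with the more restrictive assumption.

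*Discontinuation is not exclusion.* This also stands. The text below Fig. 3 does not say that outcome collection ends or that discontinued patients leave the analysis. Exclusion follows only if no 12-month SBP is obtained. What an article leaves to the full protocol on this is not an error, so wording here would be a clarification.

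*The discontinuation reasons do not single out the intervention arm.* A reader might infer that patients can be removed for not keeping up with home measurement or self-titration, which exist only in that arm. The text does not support this: incapacity to comply is tied to an adverse event or disease progression, and controls have trial procedures too. What is left is the open wording that allows any reason, applied by unblinded staff.

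*The substitution methods are only secondary checks.* A reader might infer that carrying the last value forward freezes the high entry reading. For anyone seen at 6 months, it uses that value instead. The mean of the series is not defined, so no error rate can be assigned to it. The fair criticism is narrower: both are single imputations, and no listed method is aimed at data missing not at random.

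**Conclusion.** The point stands for the Statistical analysis section. The primary analysis is labelled intention-to-treat, drops every randomised patient without a 12-month SBP, and describes no use of the 6-month SBP. It is valid only if missingness depends on nothing beyond arm and the model covariates.

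Bias is possible, not shown. A reader might conclude that the estimate requires data missing completely at random, or that it will favour the intervention. The documents support neither: the adjusted form needs less, and the direction depends on who leaves. With dropout by arm unknown, the assumed range runs from about +0.9 mmHg (low-SBP intervention patients leave), through 0 (same rate and SBP dependence in both arms), to about -0.4 to -1.6 mmHg (high-SBP patients leave the intervention arm only). It reaches about -3 mmHg under a 15 mmHg one-sided gap at equal 20% loss. Against a 5 mmHg target, that last figure is 3/5 = 60% of the effect sought. The choice should be settled before outcome data are seen by arm.

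**What to change.** 1. Make the primary analysis one of all randomised patients as allocated. Either fit a likelihood-based repeated-measures mixed model to 6- and 12-month SBP, with the 12-month contrast as the primary estimate, or use multiple imputation by arm that includes baseline and 6-month SBP.
2. Move the complete-case analysis to a sensitivity analysis.
3. Preferably add a delta-adjusted (not-at-random) multiple imputation, rather than rely on last-value and series-mean substitution.
4. State that 12-month SBP is sought from every randomised patient who has not withdrawn consent, including those discontinued, and is analysed as randomised.

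The cost is revised analysis wording, one clarifying sentence on follow-up and a little extra programming. The 6- and 12-month visits are already scheduled, so no new visits are needed.

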#### Control group

Patients will be informed by their GP that they will continue their usual care regarding their BP and that they will be recalled to make an appointment with a member of the research team, who will provide them with information and basic recommendations for improvement of BP control and for completing the data corresponding to the baseline visit. Subsequently, members of the research team will deliver the “*Control group booklet”* containing the patient’s code, general information and basic recommendations for improving BP control, as well as the “monthly registration sheets” for a six month period in order to register contacts related to their BP (by phone, regular or urgent consultation at the general practice or hospital consultation) during the follow-up period.

Patients in the control and intervention groups will be informed that the research team will phone them four weeks after the baseline visit to clarify any doubts raised. If necessary, on-site visits will be arranged for further clarification.

Both groups will be contacted by phone at 3 months to clarify any doubts and at 6 months a follow-up visit will be established at the PCC, where the corresponding variables will be collected. The same will be done at 12 months. The follow-up variables will be collected up to a maximum of 6 weeks after the end of the follow-up period. An extension of the study will be performed with passive follow-up at 24 months, collecting a reduced set of outcome variables as secondary variables. Participants’ flow through the trial is outlined in Fig. 3.

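### The primary analysis is labelled intention-to-treat but keeps only complete cases at 12 months, so randomised patients without that reading drop out of the estimate and any 6-month SBP they have goes unused

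*Protocol article*

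**What the plan says.** The Statistical analysis section opens with "Analysis will be on an intention-to-treat basis for complete cases". Mixed models are then to be used "to compare SBP at 12 months between the intervention and control groups", in crude and adjusted forms, with covariates listed as "baseline BP, gender, GP/PCC-random effect, diabetes, etc". No patient-level random effect or within-patient covariance is mentioned, so the text describes a model of one time point clustered by GP or centre. It is not a repeated-measures model.

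Missing data are covered by a sensitivity analysis, "which will include substitution by multiple imputation, replacement of data lost by the most recent data or by the mean of the series".

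Under Outcomes, "The primary outcome will be the change in mean SBP -mmHg- between baseline and 12 months", and a secondary outcome is "Change in mean SBP at 6 and 24 months of follow-up". The 6-month value comes from a visit planned for both arms: "at 6 months a follow-up visit will be established at the PCC, where the corresponding variables will be collected" (Participant flow through the study, Control group). Sample size consideration expects losses: "These figures will be increased by 20% to compensate for possible drop-outs and follow-up loss".

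**The concern.** The opening sentence joins two things that do not fit well together. Intention-to-treat is commonly read as all randomised patients in their allocated arm, whereas complete cases are only those with the 12-month reading. A reader of the trial report would take the headline result for the former when it is the latter.

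Randomisation protects the comparison only for the full set. The trial is unblinded. Both arms fill in monthly sheets, but controls record only contacts about their blood pressure, while intervention patients also measure it at home and adjust their own medication. Patients may leave at any time, and the researcher may discontinue them, for instance after an adverse event. The reasons for missing month 12 could therefore relate to blood pressure differently by arm, and the completers would then no longer be comparable. The 6-month SBP carries information on exactly this, and the primary estimate does not use it.

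**Working it through.** **1. The plan's own figures.** Inputs from Sample size consideration: difference 5 mmHg, SD 15 mmHg, two-sided alpha 0.05, power 90%.

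- Normal approximation: n per arm = 2 × (1.960 + 1.282)² × 15² / 5² = 2 × 10.51 × 9 = 189.2, so 190 per arm and 380 in total.
- t-test version: 190.1, so 191 per arm and 382 in total, as stated.
- 382 × 1.2 = 458.4, stated as 458.
- Loss that 458 can absorb before falling below 382: 458 − 382 = 76 patients, and 76 / 458 = 16.6%.
- Power is 90.3% with 382 analysed. At 20% loss it is 89.1% with 366 analysed. Power is not the issue.

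**2. Size of the bias in general.** Let a fraction d be missing in each arm, and let gap be the mean 12-month SBP of the missing minus that of the observed. The all-randomised arm mean equals the observed mean plus d × gap. So the crude complete-case contrast differs from the all-randomised contrast by d × (gap in the intervention arm − gap in the control arm), in absolute value. With d = 0.166 and assumed gap differences of 2, 5 and 10 mmHg:

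- 0.166 × 2 = 0.33 mmHg
- 0.166 × 5 = 0.83 mmHg
- 0.166 × 10 = 1.66 mmHg

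**3. Simulation.** SD 15 comes from the protocol. Everything else is assumed: true effect −5 mmHg at 6 and 12 months, correlation of baseline with each follow-up 0.4, 6-to-12-month correlation 0.6, and 16.7% missing month 12 in each arm. The log-odds of missing are linear in 6-month SBP, and everyone lost has a 6-month value unless stated. OR is the odds ratio for drop-out per 15 mmHg. Each scenario has 2,000,000 simulated patients, so simulation error is about 0.02 mmHg. The last column is a missing-at-random estimate using baseline and 6-month SBP.

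| Drop-out scenario | Complete-case, crude | Complete-case, baseline-adjusted | Using 6-month SBP |
|---|---|---|---|
| Unrelated to SBP | −5.00 | −5.00 | −5.01 |
| OR 2.2 in both arms | −5.00 | −5.01 | −5.01 |
| OR 1.5, intervention arm only | −5.60 | −5.43 | −4.99 |
| OR 1/1.5, intervention arm only | −4.40 | −4.57 | −5.00 |
| OR 2.2, intervention arm only | −6.07 | −5.78 | −4.98 |
| OR 1/2.2, intervention arm only | −3.90 | −4.17 | −4.97 |
| OR 2.2 intervention, 1/2.2 control | −7.15 | −6.60 | −4.99 |
| OR 1/2.2 intervention, 2.2 control | −2.83 | −3.39 | −5.00 |

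The baseline-adjusted error thus runs from about 0.4 mmHg (OR 1.5 in one arm) to 1.6 mmHg (opposite links), with either sign.

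**4. Variations on OR 2.2 in the intervention arm only.**

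- 6-to-12-month correlation 0.5 or 0.7: adjusted complete-case −5.60 or −5.98, an error of 0.6 or 1.0.
- Loss of 10% or 5%: −5.51 or −5.25.
- Half of those lost also miss month 6: complete-case −5.79, using 6-month SBP −5.36.
- All of those lost also miss month 6: both −5.77, so nothing is gained.
- Drop-out driven by baseline SBP: adjusted complete-case −4.96, crude −5.69. Adjustment alone deals with this case.
- Drop-out driven by the unseen 12-month SBP: adjusted complete-case −6.56, using 6-month SBP −6.17. The remedy helps only in part.

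**The case against.** The plan does not ignore missing data. It names multiple imputation, and if 6-month SBP is in the imputation model, that rests on the same missing-at-random assumption as a repeated-measures model and should give nearly the same answer. This stands, and it narrows the point to which analysis is primary. It does not remove the point: the headline figure stays complete-case, and the article does not say that 6-month SBP enters the imputation. The other two options, the most recent value and the series mean, are single imputations that can add bias of their own.

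The wording is also open about its restriction and may simply mean analysed as allocated among those with data. That is fair. The label is loose, but nothing is concealed. Nor is this a detail left to an unseen analysis plan, because the article states the choice.

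A reader might infer more than the documents support:

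- That the trial will overstate the benefit. Nothing in the protocol fixes the sign: with the link reversed in the intervention arm, the benefit is understated.
- That only the intervention arm carries a monthly task and so loses patients selectively. Controls also receive monthly sheets, and both arms have the same calls and visits. What differs is home measurement and self-titration.
- That the primary result is known to be biased. The drop-out odds ratios and correlations are assumptions, and with no link or an equal link there is no bias.

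**Conclusion.** The point holds as a conditional one. The stated primary set is narrower than its label suggests, and it discards information that the trial already collects. The possible error, about 0.4 to 1.6 mmHg in the baseline-adjusted estimate, is 8% to 32% of the 5 mmHg target (0.4 / 5 and 1.6 / 5). It rests on roughly 17% loss, a 6-to-12-month correlation of 0.6, arm-specific links between drop-out and 6-month SBP, and month 6 having been attended by those lost. It shrinks with less loss or weaker links. The crude form is more exposed than the adjusted one in every biased scenario tried, and the article does not say which of the two is primary. Because the size and sign cannot be known from the documents, and a suitable sensitivity analysis is already named, this is a recommended improvement and not a must-fix.

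**What to change.** Replace the restriction to complete cases with a primary analysis of all randomised patients in their allocated arm. Either of two routes would do:

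1. A likelihood-based mixed model of SBP at baseline, 6 and 12 months, with arm-by-visit effects, within-patient correlation and the planned GP/PCC random effect. The 12-month arm contrast is the primary result.
2. The multiple imputation already planned, promoted to primary, with 6-month SBP, baseline SBP and arm stated as part of the imputation model.

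Keep the complete-case comparison at 12 months as a sensitivity analysis, and add one for data missing not at random, for example by shifting the imputed values separately by arm over a stated range.

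The cost is wording and analysis time. No new visit, measurement or patient is needed. The result would rely on data being missing at random given observed SBP, which is a weaker assumption than complete-case analysis makes. There is no gain for patients who also miss month 6, and little gain in precision otherwise.
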